#### Maternal measures

##### Demographics

Basic demographic information (e.g., gender, age, primary language, household living situation, employment status, household income) is obtained via self-report from mothers.

##### Acculturation (Baseline only)

We ask Hispanic mothers to complete the Brief Acculturation Rating Scale for Mexican Americans II [45]. This 12-item scale measures acculturation along three factors (language, ethnic identity, and ethnic interaction) and has been used with Mexican Americans and individuals of Puerto Rican decent [45,46].

##### Feeding practices

Mothers complete the 19-item Caregiver’s Feeding Styles Questionnaire, a well validated and frequently used measure of the demandingness and responsiveness of parental feeding practices [47-49].

##### Additional maternal variables

We are assessing 5 potential moderators that might influence treatment response including a 15-item food insecurity questionnaire [50], the 4-item Perceived Stress Scale [51], a 2-item maternal depression screening tool [52], the 15-question Health Care Climate Questionnaire [53] that assesses the mother’s perceptions of the degree to which her child’s medical team provides autonomy support, and an abbreviated version of the Neighborhood Environment Walkability Scale [54,55].

##### Process evaluation (12 months only)

At the end of the intervention period, we ask mothers to evaluate the program they received, whether they found it helpful, which components were most useful, and whether they would refer a friend to receive the same program.

#### Medical teamlet measures

After obtaining consent and prior to BMC training, clinicians, and nurses completed a set of questionnaires that address self-efficacy, outcome value and outcome expectancy related to obesity prevention in children, clinician-parent interactions around obesity, as well as their experience and thoughts regarding BMC and knowledge regarding obesity.

##### Demographic survey

Job status (full time vs. part time), tenure (length of time in the PCC), number of years since receiving highest degree, and Spanish fluency are assessed via self-report.

##### The office weight management survey

This 52-question instrument assessed clinical goals for obesity prevention/reversal, time spent in obesity-related activities, self-efficacy, outcome value and expectancy and barriers to obesity prevention/reversal. The instrument was made specific for obesity from a general pediatric instrument [56] and from the recommendations of the AAP’s Obesity Task Force.

##### Healthy living questionnaire

This 20-item questionnaire examines clinician knowledge surrounding healthy behaviors for two year olds and is based upon the 2007 AAP Guidelines.

##### Hope and conscientiousness

The personality traits of hope and conscientiousness have been found in previous research to predict goal directed behavior by primary care clinicians [57]. We assess these traits among clinicians and nurses at baseline using the 4 agency and 4 pathway statements of the Hope Scale [58] and the Five Factor Inventory [59] in addition to a 10-item obstacles scale specifically related to work obstacles in a primary care setting [57].

#### Adherence and treatment fidelity

We are recording the number of BMC visits completed in total and by each member of the medical teamlet (i.e., number of BMC doses delivered; number of signed action plans) and by CHWs, as well as the number of telephone contacts completed by CHWs and study staff.

On each post-clinic visit phone call that is completed within a week of each BMC dose, study staff are assessing mothers’ perceptions of their clinic encounter. Specifically, mothers are asked to respond no, somewhat, or yes to whether the doctor or nurse 1) reviewed their responses to the Steps to Growing Up Healthy Survey, 2) told them some things they were doing right in terms of their child’s eating and exercise habits, 3) talked to them about areas in which they could make changes to improve their child’s nutrition and physical activity, and 4) asked in what specific area they would like to make changes in. Mothers are also asked if the doctor or nurse selected the behavioral goal or if this was decided upon together.

### Retention

Proactive efforts are made to retain families for the 12-month study period. To aid in locating families for follow-up assessments, contact information (name, address, and phone number) of a family member and friend is obtained at the time of enrollment and at the time of each visit. As part of the Steps to Growing Up Health study, families are given an honorarium of $25 at baseline and at 12 months for completing these assessments visits (for a possible total of $50). Families in BMC + Phone and BMC + Home receive $5 per telephone call or home visit for a possible additional total of $60.

### Sample size and power

The primary outcome is change in child’s BMI percentile from baseline to 12 months. We hypothesize that both BMC + Phone and BMC + Home will reduce BMI percentiles compared to BMC. Assuming no change in BMI percentile for BMC and a 2.5 percentile change in BMI for BMC + Phone (i.e., 90^th%^ to 87.5^th%^) and a 5 percentile change in BMI in BMC + Home (i.e., 90^th%^ to 85^th%^), with an alpha of 0.05 and an ANCOVA with 3 treatment groups, we need 34 children per group to have 0.85 power to be able to perform 3 contrasts: BMC vs. BMC + Phone, BMC vs. BMC + Home, and BMC + Phone vs. BMC + Home. We plan to recruit 50 children per arm to allow for a 15% dropout rate. Even if 25% of participants drop out we will have 80% power to test our primary aims.

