## Methods/Design

### Overview and hypotheses

Latino and Black mother-child dyads (targeted *n* = 150) are recruited for this 12-month randomized trial at an urban based pediatric primary care clinic (Figure 1). Participating dyads are assigned with equal probability to one of three treatment conditions: 1) brief motivational counseling (BMC) alone delivered by the child’s medical team; 2) BMC plus monthly phone calls by a CHW (BMC + Phone); or 3) BMC plus monthly home visits by a CHW (BMC + Home). Dyads are assessed at baseline and 12 months. The primary outcome is change in the child’s BMI percentile. We hypothesize that over the 12-month period both BMC + Phone and BMC + Home will produce greater reductions in BMI percentiles than BMC and that BMC + Home will produce greater reductions in BMI percentiles than BMC + Phone. The study protocol was reviewed by the Scientific Review Committee at Connecticut Children’s Medical Center (CCMC) in Hartford, CT and received full approval by CCMC’s Institutional Review Board.

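### The sample-size figures conflict: 34 per arm for 0.85 power does not fit 80% power at 25% dropout from 50 per arm

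*Protocol article*

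**What the plan says.** All the figures stand in one paragraph of the protocol article, Sample size and power.

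- **Effects:** "Assuming no change in BMI percentile for BMC", "a 2.5 percentile change in BMI for BMC + Phone" and "a 5 percentile change in BMI in BMC + Home".
- **Test:** "with an alpha of 0.05 and an ANCOVA with 3 treatment groups".
- **Requirement:** "we need 34 children per group to have 0.85 power to be able to perform 3 contrasts". These are the three pairwise comparisons of the arms.
- **Recruitment:** "We plan to recruit 50 children per arm to allow for a 15% dropout rate".
- **Power at higher loss:** "Even if 25% of participants drop out we will have 80% power to test our primary aims".

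Overview and hypotheses confirms equal allocation ("Participating dyads are assigned with equal probability to one of three treatment conditions") and a total of 150, so 50 per arm is firm. The paragraph gives no SD, baseline-to-follow-up correlation or sidedness.

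**The concern.** With alpha, effect and variance held fixed, power rises with the number of children analysed. The paragraph has it falling: 0.85 with 34 per arm, but 0.80 with the 37 or 38 left after 25% dropout. The step from 34 to 50 is also not a 15% allowance.

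At stake is how many completers per arm the trial needs for the power it claims. A reader who takes 34 as the requirement would think that 16 of 50 per arm can be lost with 0.85 power intact. If the other two statements are the correct ones, power at that point is about 0.76.

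**Working it through.** **Inputs (Sample size and power):** 34 per group for 0.85; 50 per arm; dropout 15% and 25%; 0.80 at 25%; alpha 0.05, taken as two-sided because the text does not say.

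**1. Dropout arithmetic**

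- Recruitment needed for 34 completers at 15% loss: 34/(1 − 0.15) = 40. The cruder 34 × 1.15 = 39.1 also rounds up to 40. The stated 50 is not reproduced.
- At 25% loss: 34/0.75 = 45.3, so 46.
- Left from 50: 50 × 0.85 = 42.5 at 15%, and 50 × 0.75 = 37.5 at 25%. Both exceed 34.
- Loss that takes 50 down to 34: 1 − 34/50 = 32%.

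**2. Power without knowing the SD**

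For a two-group contrast with n per arm and standardised effect d, power ≈ Φ(d√(n/2) − 1.960). One (n, power) pair fixes d, and power at any other n follows. The missing SD therefore does not matter for this check.

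*Taking 34 = 0.85 as correct.* d√(34/2) = 1.960 + 1.036 = 2.996.

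- At 37.5: 2.996 × √(37.5/34) = 3.147, and Φ(3.147 − 1.960) = 0.88.
- n for 0.80: 34 × (2.802/2.996)² = 29.7, so 30 per arm, which is 40% dropout from 50. (2.802 = 1.960 + 0.842.)

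*Taking 37.5 = 0.80 as correct.* d√(37.5/2) = 2.802.

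- n for 0.85: 37.5 × (2.996/2.802)² = 42.9, so 43.
- At 34: 2.802 × √(34/37.5) = 2.668, and Φ(2.668 − 1.960) = 0.76.

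**3. Does the choice of test matter?**

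The first calibration (34 = 0.85) was repeated under other readings of the test. In each case the plan states 0.80 for 37 to 38 per arm.

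| Test | Power at 37 to 38 per arm |
|---|---|
| Two-sided 0.05, normal | 0.878 to 0.886 |
| One-sided 0.05 | 0.875 to 0.883 |
| Two-sided 0.05/3 | 0.882 to 0.891 |
| Noncentral t, two groups | 0.879 to 0.887 |
| Three-group F, one covariate | 0.881 to 0.890 |
| All three contrasts significant (simulated) | 0.887 to 0.895 |

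At 42 per arm (15% dropout) the same calibration gives about 0.92 (0.916 by t, 0.920 by F). Power of 0.80 is reached at about 30 to 31 per arm, which is 38% to 40% dropout.

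In the other direction, with 0.80 fixed at 37, 37.5 or 38 per arm, 0.85 needs 42.2, 42.8 or 43.4 (noncentral t, df 3n − 4) or 41.8, 42.4 or 42.9 (F). Power at 34 is 0.75 to 0.77.

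**4. Which figure is out of line?**

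The last two statements agree with each other. If 42.5 per arm (50 less 15%) gives 0.85, then 37.5 (50 less 25%) gives 0.804 two-sided, 0.809 one-sided, 0.796 at 0.05/3 and 0.799 for the F test. Powering on winning all three contrasts gives 0.784, with 0.72 at 34. So 34 is the figure that does not fit the other two.

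**The case against.** **The 80% could be a floor, and 50 deliberate over-recruitment.** On that reading 34 gives 0.85, 50 is more than enough for 15% dropout, and power at 25% dropout is at least 0.80. No sentence is then formally false. But the paragraph attributes 50 to 15% dropout, and it introduces the 25% case as a worse scenario in which power is 80%, after quoting 0.85. Rounding up could explain 50. It does not explain a power figure below the one given for fewer children.

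**The two power figures could refer to different tests.** Suppose 0.85 is the power of each 2.5-point contrast at 34 per arm (d = 0.734), and 80% is the power to win all three together. Simulated joint power is then 0.70 at 34, 0.77 at 37.5 and 0.84 at 42.5, so a joint figure below 0.85 at 37.5 is possible. It still does not reproduce 0.80, and the primary aims are the same three contrasts. If two tests were meant, the paragraph has to say so.

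**The consequences are limited.** This stands in large part. Nothing in the protocol makes 34 completers a retention target or threshold. The Primary analysis section includes all randomised children, imputes BMI percentile change for dropouts from chart heights and weights, and adds a completer analysis. On either calibration, 50 per arm gives about 0.85 or more at 15% dropout and 0.80 or more at 25%.

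**Conclusion.** The concern holds. For any one test with fixed alpha, effect and variance, 34 per arm for 0.85 and 80% power at 25% dropout from 50 per arm conflict, and 50 is not 34 inflated for 15%.

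- If 34 is right, power at 25% dropout is understated by about 8 points (0.88 against 0.80), and the dropout allowance is 32%, not 15%.
- If the dropout statements are right, the requirement is understated by 8 to 9 completers per arm (42 to 43 against 34), and power at 34 is overstated by about 9 points (0.76 against 0.85).

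The conclusion assumes that both power figures refer to the same test and that 80% is meant as the power at that loss. It does not need the SD. The document cannot settle which figure is wrong, though the agreement between the 15% and 25% statements points to 34. The practical effect is modest because 50 per arm suffices either way; what fails is the stated basis for it.

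**What to change.** Re-run the calculation and replace the paragraph with one consistent set: the test that carries the power, its sidedness and any multiplicity adjustment, the residual SD (with the baseline-to-follow-up correlation if used), completers needed per arm, and power at 15% and 25% dropout.

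- If the re-run supports the 15% and 25% statements, replace 34 by the recalculated number, about 42 to 43 completers per arm for 0.85, and note that 34 would give about 0.76.
- If it supports 34, state the allowance as 32% instead of 15%, and power at 25% dropout as about 88% instead of 80%.
- If 0.85 and 80% refer to different tests, name each one.

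The figures above come from calibration, so those from the re-run should be the ones printed. Keep 50 per arm. The cost is the wording of one paragraph and possibly a less favourable completer requirement; enrolment and analysis do not change.

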### Statistical analysis

#### Primary analysis

We will use an-intent-to-treat approach to data analysis. All randomized children will be included in the analyses regardless of whether they receive any actual intervention. We will impute BMI percentile change among attritors using their historical heights and weights obtained through chart review; however, we also will conduct treatment completer analyses using only complete cases. Baseline variables (e.g., demographics) will be compared between intervention groups using chi-square statistics and *t*-tests to determine if any group differences exist despite randomization. Baseline variables that differ between groups will be included as covariates in subsequent analyses.

Repeated measures analysis of variance models will be conducted to address the research questions. In the primary analysis, the dependent variable will be BMI percentile. In this model, the within-subject factor will be time, which will include 2 levels (baseline and 12 months). Between-subjects factors will include treatment group (BMC, BMC + Phone, and BMC + Home). Demographic variables that are found to differ across groups will be included as covariates.

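### Covariates for the primary model are chosen by tests of baseline differences between randomised groups, which leaves the model unfixed and ignores prognostic value

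*Protocol article*

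**What the plan says.** In the protocol article, the Primary analysis section sets out a screening step: "Baseline variables (e.g., demographics) will be compared between intervention groups using chi-square statistics and" t-tests, with the stated aim "to determine if any group differences exist despite randomization". The consequence follows at once: "Baseline variables that differ between groups will be included as covariates in subsequent analyses".

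The next paragraph repeats the rule inside the description of the primary model, with a narrower pool of candidates: "Demographic variables that are found to differ across groups will be included as covariates".

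The only terms fixed in advance are treatment group and time: "In this model, the within-subject factor will be time, which will include 2 levels (baseline and 12 months"). Baseline BMI percentile is therefore one of the two levels of the outcome and not a covariate. No threshold is given for when groups differ, and no covariate is named on prognostic grounds. The Demographics section gives examples of what is collected: "gender, age, primary language, household living situation, employment status, household income".

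**The concern.** Allocation is random: "Participating dyads are assigned with equal probability to one of three treatment conditions". A baseline difference between arms is then a chance event, and a test of it addresses a hypothesis already known to be true. Whether a variable happens to differ says nothing about whether it predicts BMI percentile, yet that link alone determines whether adjustment improves the estimate.

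Three things are at stake.

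- **The primary model is not defined in advance.** Its covariates depend on the baseline data, on a threshold that is not stated, and on which of the two candidate pools applies (all baseline variables or demographics only).
- **The tests are not fully specified.** A t-test compares two groups and the trial has three arms, so a continuous variable could be tested once in some other form or up to three times.
- **The way a selected covariate enters is not stated.** With two time points, the group-by-time test is a test on the change score. A time-constant covariate entered as a main effect cancels from that change and leaves the test as it was. It matters only if crossed with time. Depending on the choice, the rule does nothing to the primary test or changes it.

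This is not a detail left to an analysis plan: the article states the rule, twice.

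**Working it through.** The plan attaches no figure to this rule. Its nearest number, 34 children per group in Sample size and power, cannot be reproduced because no standard deviation is given, and this point does not depend on it.

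**1. Chance that at least one covariate enters purely by chance**

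Inputs: six example demographics (Demographics section); a threshold of 0.05 and independent tests (both assumed).

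- One test per variable: 1 − 0.95^6 = 1 − 0.735 = 0.265, about 26%.
- If primary language, living situation, employment status and gender get one chi-square test each, and age and household income get three pairwise t-tests each, a per-variable rate is needed for any of three pairwise tests. Simulation at 50 per arm (20,000 runs) gives 0.124; an approximate value is 0.122.
  - With 0.122: 1 − 0.95^4 × 0.878^2 = 1 − 0.8145 × 0.7709 = 0.372.
  - With 0.124: 1 − 0.8145 × 0.876^2 = 1 − 0.8145 × 0.7674 = 0.375.
  - Either way, about 37%.

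Under the wider sentence covering all baseline variables, the count is open. For assumed counts:

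| Candidates | One test each | All tested pairwise |
|---|---|---|
| 10 | 0.401 | 0.735 |
| 15 | 0.537 | 0.864 |
| 20 | 0.642 | 0.930 |

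The last column overstates the chance, because it treats every variable as continuous.

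**2. Chance that a prognostic variable is left out**

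Selection does not depend on the link to outcome, so the chance is 1 − 0.05 = 0.95 with one test, or 1 − 0.124 = 0.876 with three pairwise tests: about 88% to 95%.

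**3. Effect on precision and type I error**

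One two-arm contrast was simulated with 42 per arm (50 × 0.85 = 42.5, the planned recruitment less the planned dropout), one baseline covariate with assumed correlation r to the analysed outcome, no treatment effect, and 6,000 runs per setting. Standard errors are in SD units.

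| r | SE, chosen by test | SE, fixed in advance | Ratio | Type I error, chosen by test | Type I error, fixed in advance |
|---|---|---|---|---|---|
| 0 | 0.2182 | 0.2196 | 0.99 | 0.0482 | 0.0495 |
| 0.3 | 0.2152 | 0.2094 | 1.03 | 0.0478 | 0.0495 |
| 0.5 | 0.2100 | 0.1901 | 1.10 | 0.0432 | 0.0495 |
| 0.7 | 0.2020 | 0.1568 | 1.29 | 0.0348 | 0.0495 |

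The Monte Carlo error of a rate near 0.05 is √(0.05 × 0.95 / 6000) = 0.0028. The rate at r = 0.3 is therefore indistinguishable from 0.05. Those at 0.5 and 0.7 lie below it. No setting shows inflation.

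**4. Where a time-constant covariate acts**

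Write the outcome at time t as group effect + time effect + group-by-time effect + βX + error. The 12-month value minus the baseline value removes βX, so the group-by-time test is unchanged. With a time-specific coefficient β_t, the term (β_12 − β_0)X stays in the change and the test is affected.

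**The case against.** The case for leaving the rule alone has real substance.

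- **It was written in advance and uses baseline data only.** This stands. A reader might infer that covariates could be picked by looking at outcomes; the text gives outcomes no role in the choice.
- **It does no harm to validity.** This also stands. A reader might infer inflated type I error from a data-dependent model, but the simulation shows a rate at or slightly below nominal. A covariate admitted by chance does not bias the comparison, and a binary or continuous one costs one degree of freedom among at least 3 × 42 = 126 children.
- **The chance of spurious entry should not be put at 54% to 86%.** A reader might reach those figures by counting about 15 baseline variables. The sentence within the primary model restricts candidates to demographics, several of which are categorical and need only one test. Acculturation, one of the wider candidates, is asked only of Hispanic mothers and could not serve as a whole-sample covariate. The higher figures belong only to the broader sentence, with an assumed count.
- **The lost precision is hypothetical.** Partly right. The documents do not show that any listed variable predicts change, and BMI percentile is already age- and sex-specific, so those two are weak candidates. At r = 0.3 the loss is small.
- **A main-effect covariate cannot disturb the primary test.** Correct, but the article does not say that this is how covariates enter. If it is, the rule achieves nothing for the primary comparison.

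None of this gives the rule a benefit. The tests remain uninformative and the model remains open.

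**Conclusion.** The point holds as a matter of model specification and efficiency. The protocol commits to a selection rule driven by chance imbalance, so the covariates of the primary model are unknown until baseline data are in, and a useful predictor is omitted in about 88% to 95% of randomisations.

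The 26% and 37% figures measure how often the model would be altered by chance; they do not measure bias. They rest on a 0.05 threshold, independent tests and the six example demographics, and the second also on pairwise testing of age and income.

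The standard-error losses, about 3%, 10% and 29% at r = 0.3, 0.5 and 0.7, rest on assumed correlations for one covariate that acts on the analysed outcome. The change is worth making, but the trial's validity does not hang on it.

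**What to change.** Delete both sentences that admit covariates by baseline testing, and replace the primary model as follows.

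- **Primary analysis:** ANCOVA of 12-month BMI percentile on treatment group (three levels), with baseline BMI percentile as covariate. This matches the power statement, which is worked "with an alpha of 0.05 and an ANCOVA with 3 treatment groups", and the dose-response regression in Secondary analyses, which already controls for baseline BMI percentile. It also removes the question of whether a covariate is crossed with time.
- **Further covariates, if any:** a short list chosen for expected prognostic value, fixed before outcome data are seen, and used whether or not the arms differ on them.
- **Baseline table:** descriptive, without p-values.
- **Imbalance-driven adjustment:** if wanted, keep it as a labelled sensitivity analysis.

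Cost: this is more than a wording edit, because the stated primary model changes from repeated measures ANOVA to ANCOVA, and a few degrees of freedom are used. Data collection and sample size are unaffected.
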